Several observational studies have reported on vitamin D status and respiratory infection. A Turkish case-control study found that serum 25OHD levels were lower in neonatal cases of acute lower respiratory infection (23 nmol/L) than age-matched controls (41 nmol/L)^66^. A Finnish cohort study found that young male soldiers with serum 25OHD levels <40 nmol/L at baseline had a 63% increased risk of absence from duty over the following 6 months as a result of a respiratory infection compared with soldiers with levels >40 nmol/L (P=0.004)^67^. A Canadian case-control study of children aged 1-25 months found no difference in mean serum 25OHD levels between cases of acute lower respiratory tract infection (77 nmol/L) and hospital controls (77 nmol/L)^68^. However this finding is probably a result of virtually all of the infants having high vitamin D diets through fortified formula or supplementation. A secondary analysis of the US NHANES III survey showed that, after adjusting for demographic and clinical characteristics, lower 25OHD levels were independently associated with self-reported upper respiratory tract infection (URI; cold and flu-like illnesses) in the past few days (compared to ≥75 nmol/L group: OR 1.36 [95%CI, 1.01-1.84] for <25 nmol/L and OR 1.24 [95%CI, 1.07-1.43] for 25-74 nmol/L groups)^69^. In a New Zealand cohort of 112 patients admitted to hospital with CAP, median 25OHD levels were 54 nmol/L, 15 % had serum levels <30 nmol/L and low levels were significantly associated with a higher 30-day mortality (OR 12.7; [95%CI 2.2-73.3])^70^. Similarly, in a cohort consisting of over 400 adult CAP patients admitted to either Christchurch or Waikato hospitals, 67% of those with 25OHD levels > 50 nmol/L had complete resolution of pulmonary infiltrate as assessed by chest x-ray at 6 weeks after hospital discharge, while only 53% of patients with levels <25 nmol/L and 56% of patients with levels between 25-50 nmol/L had complete resolution. In addition, a higher mortality rate (11%) was observed for those patients that had 25OHD levels < 25 nmol/L and fewer reported being back to normal activity (50%) compared to those that had levels > 50 nmol/L (4% mortality and 61% reported return to normal activity)(unpublished).

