**5. STATISTICS**

**5.1. Sample Size**

The primary outcome measure is to compare the resolution of inflammatory infiltrate on a follow-up chest x-ray at 6 weeks post-study treatment between the vitamin D and placebo arms. These sample size calculations are based on an uncorrected chi square test. To detect an increase from 50% to 70% for clear chest x-rays and assuming an 80% retention rate, 180 participants per arm would be required for a power of 0.8. In addition, we aim to have a high proportion of deficient participants within the study cohort to increase the possibility of seeing an effect. We have calculated we will need to recruit ≈120 participants with deficient vitamin D levels at baseline (i.e. < 25 nmol/L). Thus, based on our previous findings and the data from the National Nutritional Survey^29^ up to 400 CAP patients may need to be recruited to get a sufficient number of deficient participants.

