**5.2. Statistical Analysis**

All randomised participants will be included in the primary analysis. Data will be analysed on an intention to treat basis with dropout events reported on and examined for differential compliance between treatment and placebo arms. Primary analysis will be logistic regression of clear chest X-ray on treatment arm with covariates for age (grouped) and gender and if appropriate severity and comorbidities. Additional analyses will include covariates for initial 25OHD level and 25OHD level during the study and stratified analyses by 25OHD level at baseline; deficient (<25nm/l) and insufficient (<50nm/L). All data will be analysed in R (Vienna, Austria) or SAS (NC,USA).

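### The baseline 25OHD strata in Section 5.2 are nested (<25 inside <50 nmol/L), so the additional analysis does not cleanly show whether the treatment effect differs by vitamin D status

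*Protocol*

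**What the plan says.** Protocol Section 5.2 sets the main model first: "Primary analysis will be logistic regression of clear chest X-ray on treatment arm with covariates for age (grouped) and gender", with severity and comorbidities added if appropriate, on all randomised participants. It then lists secondary uses of vitamin D status. One is adjustment: "Additional analyses will include covariates for initial 25OHD level and 25OHD level during the study". The other is "stratified analyses by 25OHD level at baseline; deficient (<25nm/l) and insufficient (<50nm/L"). The unit is evidently nmol/L, as elsewhere in the protocol.

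Section 5.1 explains why deficiency matters to the design: "We have calculated we will need to recruit ≈120 participants with deficient vitamin D levels at baseline". Section 3.7.1 puts this at about 30% of the cohort and lets enrolment run on from 360 to at most 400 to reach it, with the stated aim of making an effect easier to detect.

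Section 2.3.3 describes an earlier cohort from two New Zealand hospitals in three separate bands. Complete resolution was 67% above 50 nmol/L, but "only 53% of patients with levels <25 nmol/L and 56% of patients with levels between 25-50 nmol/L had complete resolution".

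**The concern.** Strata used to ask whether an effect varies with a baseline factor should not overlap and should together cover everyone. The two named here do neither on a plain reading. The <25 group lies wholly inside the <50 group, so the two estimates share participants and are correlated. A benefit confined to the deficient would carry over into the <50 result and could be reported as a benefit in insufficiency generally. The band that would settle the matter, 25 to <50, is not reported separately, and no result at 50 or above is named for comparison.

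This is more than tidiness here. Recruitment is steered towards deficient patients, and the stratified analysis is the only one listed that estimates the treatment effect by vitamin D status; elsewhere 25OHD appears as a covariate.

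**Working it through.** The protocol gives no figure for this analysis, so there is none to reproduce. The 180 per arm in Section 5.1 belongs to the overall comparison and does not enter below. The check has three parts: how much the groups overlap, how far an effect would carry over, and what a cleaner comparison could detect.

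**Formulas**
- Share of the <50 group that is deficient: s = n(<25) / n(<50).
- Correlation between the two estimates: about √s, assuming similar per-participant variance and equal allocation in both groups.
- Apparent effect in the <50 group if the effect is 20 points below 25 and zero from 25 to <50: 20 × s. The 20 points is the planning difference in Section 5.1 ("To detect an increase from 50% to 70% for clear chest x-rays"); confining it to the deficient is hypothetical.

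**Scenario A: planning figures.** Inputs are 120 deficient and 360 to 400 enrolled (Sections 3.7.1 and 5.1). The share below 50 nmol/L is not given for this trial; I assume 60% to 80%.
- Highest overlap: n(<50) = 0.60 × 360 = 216; s = 120/216 = 0.556; √s = 0.75; apparent effect 11.1 points.
- Lowest overlap: n(<50) = 0.80 × 400 = 320; s = 120/320 = 0.375; √s = 0.61; apparent effect 7.5 points.
- In neither named group: from 0.20 × 360 = 72 to 0.40 × 400 = 160 participants, or 20% to 40%.

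**Scenario B: cohort in Section 2.2.3** (median 30 nmol/L, 26% at or below 20), lognormal assumed.
- σ = ln(30/20)/0.643 = 0.63.
- P(<25) = Φ(ln(25/30)/0.63) = 0.386; P(<50) = Φ(ln(50/30)/0.63) = 0.791.
- s = 0.386/0.791 = 0.49; √s = 0.70; apparent effect 9.8 points; about 21% in neither group.

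**Scenario C: the 112-patient cohort in Section 2.3.3** (median 54 nmol/L, 15% below 30), lognormal assumed.
- σ = ln(54/30)/1.036 = 0.57.
- P(<25) = about 0.09; P(<50) = about 0.45.
- s = about 0.20; √s = 0.44; apparent effect about 4 points; about 55% in neither group.

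| Scenario | s | Correlation | Apparent effect in <50 | In neither named group |
|---|---|---|---|---|
| A | 0.38–0.56 | 0.61–0.75 | 7.5–11 points | 20–40% |
| B | 0.49 | 0.70 | 10 points | 21% |
| C | 0.20 | 0.44 | 4 points | 55% |

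**What a clean comparison could detect.** Take 120 deficient and 240 to 280 others with the protocol's 80% retention: 48 per arm deficient and 96 to 112 per arm in the rest. Assume 50% versus 70% in the deficient, 50% in both arms of the rest, and two-sided 5% (the protocol states no alpha).
- With 112 per arm in the rest, the variance of the difference between the two risk differences is (0.25 + 0.21)/48 + (0.25 + 0.25)/112 = 0.01405; SE = 0.1185. Power = Φ(0.20/0.1185 − 1.96) = Φ(−0.27) = 0.39.
- With 96 per arm in the rest, SE = 0.1216 and power = 0.38.
- The logit scale, and a 60% rate in both arms of the rest, give 0.37 to 0.40.
- Within the deficient group alone, 50% versus 70% with 48 per arm has power of about 0.52.

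**The case against.** The strongest reply is that Section 5.2 may be naming two cut-points rather than two groups: <25 against >=25, and separately <50 against >=50. Each split is then exclusive and exhaustive, and participants at 50 or above do appear. Section 2.2.3 uses the same labels cumulatively when describing the national survey, which may explain the wording. This reading is possible, and it would answer the gap at 50 or above. It would still leave the deficient inside the <50 group and the 25 to <50 band unreported.

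Several stronger readings are tempting, and the document does not support them.
- A reader might infer that participants at 50 or above are dropped. They are not: they stay in the primary analysis and the covariate analyses, and are absent only from the named strata.
- A reader might count the missing interaction test as an error. That detail is commonly left to a statistical analysis plan, which is not at hand, and Section 5.2 does not rule such a test out. It belongs in the remedy, not the charge.
- A reader might say that no effect is expected at 50 or above. Nothing in the protocol says so; Section 3.4 doses to reach about 80–100 nmol/L, so some participants above 50 could benefit on that rationale.
- A reader might say the trial cannot show dependence on deficiency. Baseline 25OHD is measured, so any bands could be formed later. The difficulty is that bands chosen after seeing results carry less weight.

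It is also fair that the three bands in Section 2.3.3 describe an observational cohort and do not bind this trial, that their visible break near 50 makes a pooled <50 group defensible as one summary, and that Section 3.1 sets no effect-modification objective. Scenario B's 39% deficient sits above the roughly 30% the protocol aims for, so no single scenario should be taken as the answer.

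**Conclusion.** The point holds as a defect in the stated definition of an additional analysis. As written, the strata are nested, do not isolate 25 to <50 nmol/L and name no group at 50 or above, so they do not cleanly show whether the effect differs by vitamin D status in a trial that enriches for deficiency. The primary analysis and its sample size are untouched.

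The size is a range, not a figure: under a hypothetical 20-point effect confined to the deficient, about 4 to 11 points would appear in the <50 group. That rests on the assumed 25OHD distribution of recruits (deficient participants being about 20% to 56% of the <50 group), on the lognormal shape in two scenarios, and on the assumed 60% to 80% below 50 in the third. The change is worth making before results are known, but it does not threaten the trial's main conclusion.

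**What to change.** In Section 5.2, replace the two strata with the bands <25, 25 to <50 and >=50 nmol/L. These follow the cohort bands in Section 2.3.3, with a value of exactly 50 assigned to the top band. State that stratum estimates with 95% confidence intervals are exploratory, and that effect modification will be judged by a treatment-by-baseline-25OHD term in the logistic model, preferably with 25OHD continuous (for example on the log scale). If a pooled <50 result is still wanted, it can be shown as a labelled summary beside the bands.

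The cost is one sentence. No new data, visits or participants are needed. The price is statistical: estimates in the smaller bands will be imprecise, and power for a deficient-versus-rest interaction is only about 40% under the assumptions above. A non-significant interaction should therefore not be reported as evidence that the effect is the same at all levels.

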**6. DATA MANAGEMENT**

All data will be double-entered into an electronic database by trained research staff. Macros and interim tabulations will be used to check data ranges and consistency.

**7. ETHICS**

**7.1. Ethics Committee Approval**

The protocol, informed consent form, participant information sheet, questionnaires and proposed advertising material has been approved by the Southern Health and Disability Ethics Committee-13/STH/41. The Investigator will submit and, where necessary, obtain approval from the committee for all substantial amendments to the original approved documents.

**7.2. Participant Consent**

Potential participants asked to participate in the study are entitled to choose whether or not to take part. Their decision is voluntary and they should be competent to understand what is involved. Consent forms are designed to assure the protection of participant rights. Written informed consent will be obtained from each participant before enrolment in the study.

Participants will receive adequate verbal and written information in English. All of our forms and questionnaires are written in English and we are not confident we can get adequate interpreters for other languages in accordance with good clinical practice, therefore it will be a requirement that all participants are able to comprehend and communicate in English. This language requirement should not unduly disadvantage any ethnic group from participating in the study. The verbal explanation will cover all the elements specified in the written information provided for patients. The investigator or co-worker will inform the patient of the aims, methods, anticipated benefits and potential hazards of the study including any discomfort it may entail. Participants will be given every opportunity to clarify any points they do not understand and, if necessary, ask for more information. Participants are entitled to withdraw their consent to participate at any time without penalty or loss of benefits to which they are otherwise entitled.

**7.3. Participant Confidentiality**

The research staff will ensure that the participants’ anonymity is maintained. The participants will be identified by name, address, date of birth and a participants ID number. All documents will be stored securely and only accessible by trial staff and authorised personnel. The data will be anonomised as soon as it is practical to do so. Any data or samples that relate to participants that leave the study site will be identified by study number only.

**8. PUBLICATION POLICY**

The principal investigator will co-ordinate dissemination of data from this study. All publications based on this study will be reviewed by each investigator prior to submission.

